**(2) Secondary endpoints:**

- Food restriction scale score at 3, 6, 12 months after operation

- Meal amount (total calories, nutrient amount)

- Body component (body weight, body mass index, muscle mass, body fat percentage)

- Nutritional outcomes (hemoglobin, protein, albumin, cholesterol)

**3. Study Design**

(1) Study design: single center, prospective, randomization

(2) Research participation period: One year after gastrectomy for early gastric cancer

(3) Data collection period: IRB approval day – 2021. 12. 31

(4) Overall study period: IRB approval day – 2022. 6. 30.

**4. Study Population**

**(1) Target disease**

Stage I gastric cancer

**(2) Inclusion criteria**

1. Patients over 19 years of age

2. Patients diagnosed with stage 1 gastric cancer before surgery

(Early gastric cancer at preoperative endoscopy or stage I at CT scan)

3, Patients scheduled to undergo distal or total gastrectomy

4. Patients who are able to use the smartphone app or a care giver living with him can use the app to actively intervene in the patient's life.

5. Patients who have written research consent

**(3) Exclusion criteria**

1. Vulnerable patients (pregnancy, a person who lacks the ability to speak)

2. Patients who cannot use the smartphone app or the active intervention of a care-giver is difficult

**(4) Drop-out criteria**

1. Patients who have not undergone distal gastrectomy or total gastrectomy

1. The pathology test result is stage II or higher after gastrectomy
2. Patients who need adjuvant chemotherapy after gastrectomy

4. The hospital stay exceeds 3 weeks due to complications

5. Patients request withdrawal of participation

6. Patients having difficulty in collecting data suitable for the purpose of the study because they have not visited at all 1, 3, 6, and 12 months

1. **Study diagram**

|  | Informed consent | |  |
| --- | --- | --- | --- |
|  |  |  |  |
|  | Screening | |  |
|  |  |  |  |
|  | Gastrectomy | |  |
|  |  |  |  |
|  | Follow-up at 1, 3, 6, 12 months after operation | |  |

| **Data** | **Preop** | **Op** | **POD5** | **POD1m** | **POD3m** | **POD6m** | **POD12m** |
| --- | --- | --- | --- | --- | --- | --- | --- |
| age, sex, height, past medical history, smoking, alcohol, concomitant medications | O |  |  |  |  |  |  |
| operating day, operation method |  | O |  |  |  |  |  |
| pathological results of gastric cancer, postoperative complications |  |  |  | O |  |  |  |
| body weight | O |  | O | O | O | O | O |
| body component such as muscle mass measured with a body composition analyzer | O |  |  | O | O | O | O |
| EORTC QLQ C30, STO22 | O* |  |  | O | O | O | O |
| Hb, Protein, Albumin, Cholesterol | O |  | O |  | O | O | O |

**6. Patient Recruitment & Registration**

(1) **Research subject recruitment method and procedure**

- For patients who have been diagnosed with stage 1 gastric cancer and are expected to undergo gastrectomy, the attending physician directly explains and obtains consent to patients who meet the selection criteria and exclusion criteria.

- The consent process for participation in the study is to be made voluntarily after the consent is explained in detail to the subject, and the subject has sufficient time to think and ask questions.

- A copy of the consent form signed by the study coordinator is provided to the subject and the original is kept.

(2) **Number of research subjects**

- In the results of the pilot study, the eating restriction score of EORTC QLQ-STO22 that was answered at 1 month postoperatively was 30 points. The drop-out rate of the entire study was 30%. Based on this, the following hypothesis was established.

- Among the EORTC STO22 items that patients in the mHealth group responded to 1 month after surgery, the score for the eating restriction item was expected to be 30±10 (mean±standard deviation). The item score for the control group was expected to be 35 points.

- alpha value: 0.05

- power: 80%

→ sample size was calculated as 65 cases in each group.

→ Considering 30% of drop-out rate, a total of 180 cases (90 cases in each group) is needed.

- If drop-outs are more than expected, the number of sample size can be adjusted through statistical advice.

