**(5) Outcome parameters**

- Comparison of food restriction scale score of EORTC QLQ C30, STO22:

Whether there is a significant difference in the mean value is evaluated by the p-value of the t-test. Since the 1st month questionnaire is the primary endpoint, it is evaluated individually and the significance of the mixed model's p-value is evaluated to see if there are overall differences in the values ​​measured several times.

- Inbody values ​​such as meal volume, BMI, muscle mass, and blood tests were compared with the average value at 3 months, and the significance was evaluated by the p-value of the mixed model to see if there was a difference overall.

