**9. Statistical Methods**

(1) **Randomization**

- Randomization generally performs permutated mixed block randomization, and is generated in a 1:1 ratio using 2 and 4 mixed block blocks. Using the nQuery Program, a randomly assigned table is created according to the stratification factor and notified through a web-based clinical research management system.

- Stratification factors: extent of gastrectomy (distal vs. total gastrectomy)

(2) **Statistical analyses**

- Patient's clinical characteristics are expressed as mean ± standard deviation or ratio using descriptive statistics.

- Significance was evaluated by t-test for continuous variables and Chi-square test for discontinuous variables.

- For the values ​​repeatedly measured at time intervals, the difference between the two groups was compared using a mixed effect model.

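### At the planned 30% drop-out, 90 enrolled per group leaves 63, not the stated 65; the figures do not correspond, though the effect on power is negligible

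*Protocol*

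**What the plan says.** The sample size is set out in section 6(2), Number of research subjects, and again in the same words in the synopsis. The inputs relate to the 1-month eating restriction score. For the mHealth group "the score for the eating restriction item was expected to be 30±10 (mean±standard deviation"), and "The item score for the control group was expected to be 35 points". The error rate is given as "alpha value: 0.05", without saying one- or two-sided, and power as 80%.

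Two results follow. First, "sample size was calculated as 65 cases in each group". Second, "Considering 30% of drop-out rate, a total of 180 cases (90 cases in each group) is needed". Because the drop-out allowance is applied after the 65, the 65 reads as the number needed once losses have been taken off.

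The 30% is the pilot's loss, 6 of 20 patients (section 1(5)). Section 6(2) also allows the sample size to be adjusted on statistical advice if drop-out exceeds expectation. No sample-size formula is named. For the analysis of the eating restriction score, section 7(5) states: "Whether there is a significant difference in the mean value is evaluated by the p-value of the t-test".

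**The concern.** The two results stand on adjacent lines and are linked by a single step, the 30% allowance. Anyone who applies that step to 65 arrives at a number other than 90, and anyone who works back from 90 arrives at a number other than 65.

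What is at stake is the coherence of the sample-size statement. As written, a trial that recruits all 180 patients and loses exactly the predicted share ends with fewer patients than the protocol says it calculated. A reader comparing the final report with the protocol would find that mismatch, and the protocol gives no formula with which to settle it.

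**Working it through.** **Inputs.** All are from section 6(2) unless noted.
- Difference: 35 − 30 = 5 points.
- SD: 10, stated for the mHealth group and taken here as common to both, so the standardised effect is 5/10 = 0.5.
- Alpha: 0.05. Two-sided is my assumption, because a one-sided calculation gives only 50 per group, far from 65.
- Power: 80%.
- Drop-out: 30%.
- Allocation: 1:1 (section 9(1)).
- Test: two-sample t-test (section 7(5)).

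**Step 1: reproduce the 65.**
- Normal approximation: n = 2 × [SD × (z₀.₉₇₅ + z₀.₈₀)/difference]² = 2 × [10 × (1.960 + 0.842)/5]² = 62.8, so 63 per group.
- Exact t-test (noncentral t): 63.8, so 64 per group.

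The stated 65 is within two patients of the first and one of the second. As a required number it is sound on the protocol's own inputs.

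**Step 2: apply the 30% allowance.** The enrolment needed is n/(1 − 0.30).

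| Number needed after drop-out | Calculation | Per group | Total |
|---|---|---|---|
| 65 (stated) | 65/0.70 = 92.9 | 93 | 186 |
| 64 (t-test minimum) | 64/0.70 = 91.4 | 92 | 184 |
| 63 (normal-approximation minimum) | 63/0.70 = 90.0 | 90 | 180 |

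The common shortcut of multiplying by 1.3 gives 65 × 1.3 = 84.5, so 85. Neither method takes 65 to 90.

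**Step 3: work back from 90.**
- 90 × 0.70 = 63 per group, 126 in total. This is 2 per group, or 4 in total, below the stated size.
- The drop-out at which 90 still yields 65 is 1 − 65/90 = 27.8%, below the planned 30%.

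**Step 4: power at difference 5, SD 10, two-sided 0.05.**

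| Per group | t-test | Normal approximation |
|---|---|---|
| 63 | 79.5% | 80.1% |
| 64 | 80.1% | 80.7% |
| 65 | 80.8% | 81.3% |

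Moving from 65 to 63 costs 80.8 − 79.5 = 1.3 points by t-test. The gap to the stated 80% is 0.5 points by t-test, and there is none by the normal approximation.

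**The case against.** The strongest reply is that nothing of consequence turns on this. The 30% comes from 6 of 20 pilot patients, with an exact 95% interval of about 12% to 54%, so the 2.2 points between 27.8% and 30% are far inside what the pilot can resolve. The t-test power of 79.5% also rounds to 80%. And 90 per group, which appears again in the synopsis study method and in section 8(1), is the figure that governs recruitment; nowhere does the protocol commit to 65 patients at analysis. All of this stands as an argument about size. It does not make the stated numbers agree.

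The adjustment clause is no answer either. It applies when drop-out is higher than expected, and the mismatch arises when drop-out is exactly as expected.

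A reader might infer two stronger things that the document does not support:
- **That the trial misses its stated 80% power on its own assumptions.** This depends on a formula and a sidedness that the protocol does not state. By the normal approximation, 63 per group meets 80%; by the planned t-test it falls half a point short.
- **That 90 was in fact derived from 63.** The exact match of 63/0.70 with 90 is suggestive, but rounding 92.9 down to 90 would explain it equally well.

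**Conclusion.** The point holds as a small arithmetic inconsistency. The stated 65, 30% and 90 cannot all stand: at 30% drop-out, 90 per group delivers 63, and 65 would need 93 per group (186 in total, 6 more than planned). This part rests only on the protocol's own figures and does not depend on the power formula.

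The consequence for power is negligible and would not alter any conclusion of the trial. The power figures assume a two-sided test and take the SD of 10 as given and common to both groups. Whether that SD is realistic is a separate question, not examined here.

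**What to change.** Keep 180 enrolled. In both section 6(2) and the synopsis, replace the line giving 65 per group and the line giving power 80%, so that neither survives to contradict the new text. Suggested wording:

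> Ninety per group, less 30% drop-out, leaves 63 evaluable per group (126 in total). For a difference of 5 points and SD 10, this gives 79.5% power by two-sided t-test at alpha 0.05 (80.1% by normal approximation).

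This names the formula and the sidedness, both now missing. The cost is a short edit in two places and a stated power very slightly below the present one. The figures of 90 per group in the synopsis study method and section 8(1) need no change.

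If the sponsor prefers to keep 65, enrolment becomes 93 per group (186 in total). That means 6 more patients and changes to the 90 and 180 wherever they appear, for a gain of 1.3 points of power by t-test. The gain hardly justifies it.

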**7. Study Assessment & Efficacy**

**(1) Data collection**

○ Demography: age, sex, name initial

○ Anthropometric information: height, body weight, body component such as muscle mass measured with a body composition analyzer

○ Past medical history: past medical history, smoking, alcohol, concomitant medications

○ Diagnostic, pathological data: operating day, operation method, pathological results of gastric cancer, postoperative complications

○ Laboratory findings: Hemoglobin, Protein, Albumin, Cholesterol

○ Questionnaires: EORTC QLQ C30, STO22

**(2) Evaluation**

Between the mHealth and face-to-face counseling groups

- Comparison of scores of EORTC QLQ-C30 and STO22 at 1, 3, 6, and 12 months postoperatively.

- Comparison of meal amount at 1, 3, 6, and 12 months postoperatively.

- Comparison of body component (BMI, muscle mass, etc) at 1, 3, 6, and 12 months postoperatively.

- Comparison of nutritional outcomes (hemoglobin, albumin, protein, cholesterol) at 1, 3, 6, and 12 months postoperatively

**(3) Evaluation method**

- PI evaluates the completion of the performance.

- When analyzing, seek advice from the statistics team if necessary.

**(4) Evaluation time point:**

- Study completion day (2022. 6. 30.)

**(5) Outcome parameters**

- Comparison of food restriction scale score of EORTC QLQ C30, STO22:

Whether there is a significant difference in the mean value is evaluated by the p-value of the t-test. Since the 1st month questionnaire is the primary endpoint, it is evaluated individually and the significance of the mixed model's p-value is evaluated to see if there are overall differences in the values ​​measured several times.

- Inbody values ​​such as meal volume, BMI, muscle mass, and blood tests were compared with the average value at 3 months, and the significance was evaluated by the p-value of the mixed model to see if there was a difference overall.

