**(2) Schedule**

| List | Screening | Follow-up | Close |
| --- | --- | --- | --- |
| Check inclusion/exclusion criteria | X |  |  |
| Demography | X |  |  |
| Diagnosis, pathological results, complications | X | X |  |
| Body component |  | X |  |
| QoL questionnaire |  | X |  |
| Nutritional parameters |  | X |  |
| Use of smartphone app. |  | X |  |
| Report |  |  | X |

(3) **Study period**

- Research participation period: One year after gastrectomy for early gastric cancer

- Data collection period: IRB approval day – 2021. 12. 31

- Overall study period: IRB approval day – 2022. 6. 30.

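### The primary t-test uses neither the stratification factor nor the scheduled pre-operative score: conservative if gastrectomy extent is prognostic, and less precise than it could be

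*Protocol*

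**What the plan says.** Protocol section 7(5), Outcome parameters, gives the test for the eating-restriction score: "Whether there is a significant difference in the mean value is evaluated by the p-value of the t-test". It then singles out the primary time point: "Since the 1st month questionnaire is the primary endpoint, it is evaluated individually". The mixed model is kept for the overall difference across the repeated measurements. Section 9(2) repeats the choice in general terms: "Significance was evaluated by t-test for continuous variables and Chi-square test for discontinuous variables". No covariate or stratum is named for any analysis.

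Two other places bear on this:

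- Section 9(1) stratifies the randomisation: "Stratification factors: extent of gastrectomy (distal vs. total gastrectomy").
- The data table under the study diagram, after section 4(4), marks the questionnaires in the pre-operative column as well as at 1, 3, 6 and 12 months (row "EORTC QLQ C30, STO22 | O", with an unexplained asterisk on the pre-operative mark). The table in section 8(2), Schedule, marks the row "QoL questionnaire" under follow-up only and leaves screening blank.

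The sample size in section 6(2) rests on an unadjusted comparison: "the score for the eating restriction item was expected to be 30±10 (mean±standard deviation") in the mHealth group, and "The item score for the control group was expected to be 35 points".

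**The concern.** Stratified blocks hold the distal/total mix nearly equal between the arms. The true sampling variance of the arm difference then no longer contains the between-stratum part of the outcome variance, but the pooled variance in an ordinary t-test still does. If extent of resection affects eating restriction, the reported standard error is too large, the interval is too wide, and the test rejects less often than its nominal 5%.

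The pre-operative score is a different matter. Leaving it out does not make the t-test wrong in a randomised trial. It gives up precision that the scheduled data could provide at no cost to patients.

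The schedules add a practical risk. If staff work from section 8(2), the pre-operative questionnaire may not be completed, and it cannot be recovered after surgery.

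**Working it through.** **Inputs from the protocol.** Difference 35 − 30 = 5; SD 10; alpha 0.05; power 80%; 65 per group, 90 per group after 30% drop-out (section 6(2)). Pilot medians and quartiles (section 1(5)): pre-operative 6.7 (6.7 to 13.3); 1 month 30.0 (13.3 to 56.7).

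**Inputs not given, so assumed.** Correlation r between the pre-operative and 1-month scores: 0.2, 0.3, 0.5. Share with total gastrectomy p = 0.25. Total-minus-distal difference D = 5, 10 or 15 points. Within-stratum SD 10, then 32 as an alternative.

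**1. The plan's own figure.** Two-sided, n = 2(1.960 + 0.842)² × 10² / 5² = 62.8, so 63 per group, or 64 with the exact t calculation. The stated 65 is reproduced to within two patients. With 30% drop-out, 90 × 0.7 = 63 evaluable per arm. The t-test then has 79.5% power (80.1% by the normal approximation), essentially the stated 80%.

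**2. Ignoring the stratum.** The between-stratum variance is p(1 − p)D² = 0.1875 D². The ratio of the t-test standard error to the correct one is √(1 + 0.1875 D² / σ²), where σ is the within-stratum SD. For σ near 32, the pilot 1-month quartiles give (56.7 − 13.3)/1.349 = 32.2 under normality, a variance of about 1035.

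| D | 0.1875 D² | Excess SE, σ = 10 | Excess SE, σ ≈ 32 |
|---|---|---|---|
| 5 | 4.69 | 2.3% | 0.2% |
| 10 | 18.75 | 9.0% | 0.9% |
| 15 | 42.19 | 19.2% | 2.0% |

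The actual two-sided error rate is 2[1 − Φ(1.96 × ratio)]. At σ = 10 this is 0.045, 0.033 and 0.019 for the three values of D, against a nominal 0.05.

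**3. Ignoring the pre-operative score.** ANCOVA multiplies the residual variance by 1 − r², so 63 per arm act like 63/(1 − r²). Power is from the noncentral t at a difference of 5 and residual SD 10√(1 − r²).

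| r | Effective n per arm | Power |
|---|---|---|
| 0 (t-test) | 63.0 | 79.5% |
| 0.2 | 65.6 | 81.1% |
| 0.3 | 69.2 | 83.1% |
| 0.5 | 84.0 | 89.5% |

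**4. The same adjustment at the pilot-implied SD.** With SD 32.2, 63 per arm and a difference of 5, power is about 14% unadjusted, 15% at r = 0.3 and 17% at r = 0.5.

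**The case against.** The t-test is valid here. Its stratum error is conservative and cannot manufacture a positive result, and the planned power is met on the protocol's own inputs. The size of the loss rests on figures that the document does not contain. What evidence there is points to a small gain: the pilot pre-operative scores are bunched near the floor, which tends to limit correlation with later scores, and at r = 0.2 the gain is 1.6 percentage points. With an SD near 32 the stratum effect almost vanishes. All of this stands. It limits the size and urgency of the point, but it does not remove it, because the protocol itself fixes the unadjusted test and so has not left adjustment open for a later plan.

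A reader might infer three stronger claims that the documents do not support:

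- **That the trial has far less power than stated because of this choice.** At a difference of 5 and SD of 10, 79.5% against 80% is no material shortfall. Any large shortfall would come from the SD assumption, which adjustment barely touches (step 4).
- **That the interval is too wide on both counts.** In the strict sense this is true only of the stratification factor. Chance imbalance in the pre-operative score costs precision and is already allowed for in the nominal error rate. It is not bias.
- **That a mixed model would rescue the drop-outs.** The pilot's six drop-outs were four patients with stage 2 or higher on final pathology and two refusals. Both are drop-out criteria in section 4(4), so such patients may have no later forms to use. Only intermittent missing forms would be recovered, and no figure is given for those.

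The section 8(2) table is also a coarse summary. It leaves screening blank for body composition and nutritional parameters too, although the data table marks both pre-operatively. The conflict on the questionnaire is real but easily tidied.

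**Conclusion.** The point holds as an inexpensive improvement to a stated method. It is not an error that threatens the validity of the result. The primary t-test overstates its standard error if gastrectomy extent is prognostic: by 2% to 19% under the assumed share, differences and within-stratum SD of 10, and by 0.2% to 2% if the SD is near 32. Leaving out the pre-operative score forgoes roughly 2 to 10 percentage points of power at the plan's difference and SD for r from 0.2 to 0.5, with the low end more plausible. The premises are firm; the magnitudes are assumption-based.

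The conclusion is the same whether the primary time point is 1 month (sections 2(1) and 7(5)) or 3 months (synopsis, Purpose). The SD assumption is a separate and larger question.

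**What to change.** In section 7(5), and in the matching line of section 9(2) and the synopsis, replace the t-test for the primary score with one of the following, adjusting for pre-operative STO22 eating-restriction score and gastrectomy extent:

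- an ANCOVA at the primary time point; or
- the treatment contrast at that time point from the mixed model already planned, with arm, visit and arm-by-visit terms.

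Keep the analysis population that the protocol otherwise defines. Who is analysed is a separate matter and should not change through this edit.

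Mark the questionnaire at screening in section 8(2) so that it agrees with the data table under the study diagram, and explain the asterisk there if no footnote exists.

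The cost is a few sentences of analysis wording and one entry in a schedule. No new data are needed if the data table is followed. The sample size need not change for this reason, and the adjustment should not be offered as a remedy for a larger SD than planned.

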| **Study method** | - Patients who are scheduled to undergo gastrectomy for stage 1 gastric cancer are randomly assigned either to the mHealth group or the face-to-face counseling group. Patients in the mHealth group (N=90) will use mobile application for 3 months after discharge and those who in the face-to-face counseling group (N=90) will receive general nutrition counseling at 1 month and 3 months after gastrectomy.  - QOL, body component, and nutritional outcomes will be compared between the two groups.  - When obtaining the consent form, the mHealth group will be provided with a simple noom instruction manual and a noom meal record guide, and will be informed of how to use it.  - In addition, individual coaching will be given through articles and messengers on how to manage post-gastrectomy such as weight, diet, and exercise on the mobile app for 3 months from the discharge date.  - Survey response on quality of life at outpatient visits 1, 3, 6, 12 months after surgery  [figure not shown]  * The allowable date of visit at 1, 3, 6, and 12 months after surgery is 1 month before and after. | | | | |
| **Intervention method** | **- mHealth group:** After being discharged from hospital, patients will receive coaching using a smartphone app for 3 months. When the patient is discharged from the hospital, he downloads the Noom app on his or her mobile phone, registers, and then uses the Noom program. In addition, a personal coach is assigned to provide appropriate coaching to the patient on the app.  **-Face-to-Face group:**　Patients will receive individual nutrition counseling from a clinical nutritionist at the hospital at 1 month and 3 months after surgery. | | | | |
| **Evaluation** | Between the mHealth and face-to-face groups  - Comparison of scores of EORTC QLQ-C30 and STO22 at 1, 3, 6, and 12 months postoperatively.  - Comparison of meal amount at 1, 3, 6, and 12 months postoperatively.  - Comparison of body component (BMI, muscle mass, etc) at 1, 3, 6, and 12 months postoperatively.  - Comparison of nutritional outcomes (hemoglobin, albumin, protein, cholesterol) at 1, 3, 6, and 12 months postoperatively | | | | |

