**(2) Dietary adaptation of the patient**

- Patients receive nutritional counseling during the hospitalization period, but when they return to their daily life after discharge, there is no separate education on how to eat and how to adjust, resulting in various trials and errors.

- In particular, after being diagnosed as a cancer patient, there are cases where people around us hear unverified stories and eat mainly with certain foods, or they may not be able to consume enough nutrition due to restrictions on certain foods.

- They are also not well aware of postgastrectomy syndrome, so they constantly experience discomfort after eating.

- This postgastrectomy syndrome is most severe in the early postoperative period and gradually relieves after dietary adaptation.

(3) **Diet management using a smartphone app**

[figure not shown]
- Currently, for weight loss, a smartphone app (Noom) is being used that keeps a daily meal diary, calculates meal calories, and provides 1:1 customized coaching service.

- Noom not only makes it easy for users to enter the food eaten during the day based on the food database, but also helps the coach in charge check daily to keep the dietary control.

- If Noom is used in the process of dietary adaptation after surgery for gastric cancer patients, it is expected that balanced nutritional intake will be achieved through appropriate dietary disorders. In addition, by providing information on gastrectomy syndrome, it is possible to reduce and prevent gastrectomy syndrome.

- Also, as Noom actively encourages exercise therapy, the patient is motivated for proper exercise.

- This is expected to reduce the patient's symptoms and improve the quality of life.

(4) **Previous literature review**

- In the past literature, the results that weight control and metabolic syndrome control were significantly improved when using a smartphone app were published in several papers.

- There have also been studies showing that breast cancer survivors, which are highly related to obesity, lose weight, increase vegetable intake, and increase exercise volume when nutritional control using a smartphone app is used.

- Regarding stomach cancer, a study on improving lung capacity with a mobile self-monitoring tool has been published, and studies related to nutrition or diet have only been introduced with protocols so far.

[figure not shown]

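### Separate 3-, 6- and 12-month comparisons are promised, but the repeated scores are judged by one overall mixed-model p-value, which cannot answer them

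*Protocol*

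**What the plan says.** **Objectives.** The Purpose row of the protocol summary lists the 6-month and the 12-month comparison as two separate secondary purposes. Section 2(2) lists "Food restriction scale score at 3, 6, 12 months after operation" as a secondary endpoint. Section 7(2) promises between-group comparisons of the questionnaire scores at 1, 3, 6 and 12 months.

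**Analysis.** Section 7(5) opens with a sentence assigning a t-test to the difference in mean score, without naming visits. It then says that month 1 is assessed on its own because it is the primary endpoint, and that "the significance of the mixed model's p-value is evaluated to see if there are overall differences in the" values measured several times. Meal volume, body measurements and blood tests are compared at 3 months and then by the same kind of overall p-value. Section 9(2) adds only that repeated values are compared between groups with a mixed effect model.

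**Timing.** Section 8(1) and the summary say: "Patients in the mHealth group (N=90) will use mobile application for 3 months after discharge". Counselling in the other arm takes place at 1 and 3 months. On symptoms, Section 1(2) says: "This postgastrectomy syndrome is most severe in the early postoperative period and gradually relieves after dietary adaptation".

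**The concern.** The rule in Section 7(5) does not match the questions in Sections 2(2) and 7(2). Two of the four visits for the scores (1 and 3 months) fall broadly within the programme and two (6 and 12 months) fall after it. A statement about overall differences says neither whether the app helps while in use nor whether any benefit lasts.

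Two misreadings could follow. A significant overall p-value driven by months 1 and 3 could be reported as a benefit lasting a year. A non-significant one could be taken as evidence against a difference at 3 months, although the protocol expressly names no individual test of the eating restriction score at that visit. The opening t-test sentence leaves open whether visit-by-visit tests are intended, so the choice could be made after the results are known.

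**Working it through.** **1. Which comparison has an expressly assigned individual test?**

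| Outcome | Comparisons promised (Section 7(2)) | Individual test named (Section 7(5)) | Left to the overall p-value |
|---|---|---|---|
| Eating restriction score | 1, 3, 6, 12 months | 1 month | 3, 6, 12 months |
| Meal volume, body composition | 1, 3, 6, 12 months | 3 months | 1, 6, 12 months |
| Blood tests | 1, 3, 6, 12 months (the data table has no blood test at month 1) | 3 months | 6, 12 months |

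Months 6 and 12 have no express individual test for any outcome.

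**2. Do those visits fall after the programme?** The app runs for 3 months from discharge, and stays beyond 3 weeks because of complications are a drop-out criterion. App use should therefore end by about 3 months and 3 weeks after surgery. With the one-month window, the 6-month visit is no earlier than month 5. Both later visits are after the programme.

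**3. The plan's own sample size.** Section 6(2) gives "alpha value: 0.05" and 80% power. For mHealth, "the score for the eating restriction item was expected to be 30±10 (mean±standard deviation"). For control, "The item score for the control group was expected to be 35 points". So the difference is 5 and the SD 10. Taking alpha as two-sided (the sidedness is not stated):

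n = 2 × (1.960 + 0.842)² × 10² / 5² = 62.8, so 63 per group (64 with the t distribution).

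The plan says: "sample size was calculated as 65 cases in each group". That agrees within 2 patients. Power at one visit is 80% with 63 and 81% with 65. I use 63 below, which is 70% of the 90 enrolled.

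**4. Power if overall means a time-averaged arm effect.** Assumptions: four equally weighted visits, 63 evaluable per arm at each, SD 10 throughout, common correlation r between visits.

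- SD of a patient's four-visit mean = 10 × √((1 + 3r)/4)
- SE of the arm difference = that SD × √(2/63)
- Power = Φ(mean difference / SE − 1.96)

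Assumed fading pattern: 5 at month 1 (the plan's target), 3.33 at month 3 (5 × 20/30, the pilot medians), 0 at months 6 and 12. The mean is 8.33/4 = 2.08 points, 42% of the target.

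| r | SD of mean | SE | 2.08/SE | Power |
|---|---|---|---|---|
| 0.3 | 6.89 | 1.228 | 1.70 | 40% |
| 0.5 | 7.91 | 1.409 | 1.48 | 32% |
| 0.7 | 8.80 | 1.569 | 1.33 | 26% |

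Other patterns at r = 0.5 (SE 1.409):

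| Differences at 1, 3, 6, 12 months | Mean | Power |
|---|---|---|
| 5, 3.33, 1.25, 1.25 (25% of month 1 persists) | 2.71 | 48% |
| 5, 3.33, 2.5, 2.5 (50% persists) | 3.33 | 66% |
| 5, 5, 5, 5 (constant) | 5.00 | 94% |

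**5. Power if overall means a joint 4-df test of any visit difference.** Noncentrality λ = (63/2) × [Σd² − r/(1 + 3r) × (Σd)²] / [100(1 − r)]. For 5, 3.33, 0, 0: Σd² = 36.11 and (Σd)² = 69.44. At r = 0.5, λ = 31.5 × (36.11 − 0.2 × 69.44)/50 = 14.0, giving 87% power. At r = 0.3 and 0.7 it is 78% and 97%. There is no such dilution, but a significant result still does not say at which visit the arms differ.

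**The case against.** **Visit-level tests may already be intended.** Section 7(2) lists every visit, Section 9(2) gives the t-test for continuous variables, and Section 7(5) opens with a t-test sentence. Together these could mean a t-test at each visit with the mixed model as an addition. The reading is possible but not clear: the next sentence singles out month 1 for individual assessment, for a reason that applies to month 1 alone.

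**Model detail belongs in a statistical analysis plan.** That is true of fixed effects and covariance, and their absence is not the point. Section 7(5) itself states which p-value judges the repeated values, and that choice does not fit the stated objectives.

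**Early effects are protected.** This stands. Month 1 is tested individually, with about 80% power on the plan's figures, and the other outcomes are compared at month 3. A reader might infer that a real early benefit would be lost and reported as no effect; the documents do not support that.

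**Dilution is not established.** A reader might also infer that the overall test necessarily dilutes an early benefit. It does so only if the p-value is a time-averaged arm effect, which the protocol does not say, and only if the difference fades. Section 1(2) and the pilot describe symptom levels, and the pilot had no control arm; neither shows that a between-arm difference shrinks. Zero at months 6 and 12 is also an extreme case. Scaling to the pilot's preoperative median leaves 6.7/30 = 22% of the effect, or 1.12 points. The mean is then (5 + 3.33 + 1.12 + 1.12)/4 = 2.64, with about 47% power at r = 0.5.

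**Conclusion.** The mismatch holds and needs no assumption about effect size: the overall p-value in Section 7(5), in either form, cannot show whether the arms differ at 6 or at 12 months, and the unspecific t-test sentence does not clearly fill the gap. For the eating restriction score the same applies to month 3.

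The loss of power is conditional. It requires a time-averaged effect and a fading difference, with assumed correlations of 0.3 to 0.7. Then power is about 26-40% with nothing persisting, and 48-66% at correlation 0.5 with 25-50% persisting. With a constant difference it is 94%, and the pooled test is the stronger one. The month-1 primary test is untouched in every case. This is a correction worth making to the secondary analyses, not a threat to the primary result.

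**What to change.** In Section 7(5), replace the overall-differences rule with this: the mixed model contains arm, visit and arm-by-visit, and the arm difference with 95% CI is reported at each scheduled visit of each outcome. For the scores these are 1, 3, 6 and 12 months; for blood tests 3, 6 and 12 months, since none is scheduled at month 1. State that the 3-, 6- and 12-month secondary conclusions rest on these visit-specific estimates and not on the pooled p-value. If an overall test is kept as a supplement, say which hypothesis it tests. Averages over pairs of visits are optional; an average of months 6 and 12 would not answer the two separate objectives.

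The change uses the same data and needs only wording. Its cost is some power if the effect is constant over the year: for a steady 5-point difference, 80% at any one visit against 94% for the four-visit average (r = 0.5, 63 per arm).

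The summary makes month 3 primary, while Sections 2(1) and 7(5) make it month 1. That is a separate contradiction, but it must be settled before month 3 can be listed as secondary.
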